# Improving eye care in residential aged care facilities using the Residential Ocular Care (ROC) model: study protocol for a multicentered, prospective, customized, and cluster randomized controlled trial in Australia

**DOI:** 10.1186/s13063-018-3025-5

**Published:** 2018-11-26

**Keywords:** Vision impairment, Residential care, Eye care model, Protocol, Trial

## Abstract

**Background:**

Older adults in residential aged care facilities have unnecessarily high levels of vision impairment (VI) which are largely treatable or correctable. However, no current comprehensive eye health service model exists in this setting in Australia. We aimed to determine the clinical, person-centered, and economic effectiveness of a novel eye care model, the Residential Ocular Care (ROC).

**Methods/design:**

This protocol describes a multicentered, prospective, randomized controlled trial. A total of 395 participants with distance vision < 6/12 (0.30 LogMAR) and/or near vision N8 (1.00 M) or worse will be recruited from 38 urban and rural aged care facilities across Victoria, Australia. Aged care facilities will be randomized (1:1) to one of two parallel groups. Participants in the ROC group will receive a comprehensive and tailored eye care pathway that includes, as necessary, refraction and spectacle provision, cataract surgery, low vision rehabilitation, and/or a referral to an ophthalmologist for funded treatment. Usual care participants will be referred for an evaluation to the eye care service associated with the facility or an eye care provider of their choice. The primary outcome will be presenting near and distance vision assessed at the two- and six-month follow-up visits, post baseline. Secondary outcomes will include vision-specific quality of life, mobility, falls, depression, and eye care utilization at two and six months. An incremental cost-effectiveness analysis will also be undertaken.

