To date, no study has evaluated the impact of providing comprehensive eye care services to individuals with a broad spectrum of ophthalmic conditions and residing in aged care facilities. Therefore, we will implement a prospective, customized, multicentered, and cluster randomized controlled trial (RCT) to evaluate the clinical, person-centered, and cost-effectiveness of a new model of eye care. We will compare the effectiveness of Residential Ocular Care (ROC) with usual care on improving presenting and best corrected near and distance vision (primary outcome) at the two- and six-month follow-up visits. Secondary outcomes will assess the effectiveness of ROC on improving vision-specific QoL, daily functioning, health-related QoL, depressive symptoms, rate of falls, and eye care utilization, compared to the usual care group at the two- and six-month visits, after baseline, and quantify the cost-effectiveness of ROC at six months after baseline.

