### Intervention

The ROC model of eye care includes an on-site eye examination by an optometrist with expertise in domiciliary and low vision care. Four intervention options will be provided to help improve vision based on the individual participants’ eye history. These include: (1) refraction and spectacle provision; (2) cataract surgery; (3) referral to an ophthalmologist for medical and surgical treatments for conditions likely to cause loss of sight or ocular discomfort; and (4) low vision rehabilitation for untreatable eye disease. If a clinical need is identified, participants will be eligible to receive more than one intervention pathway (e.g. spectacles and low vision rehabilitation aids/services). For all pathways, transportation costs for initial consultations and for up to two follow-up consultations (to either a public or private care provider) will be funded by the study.

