#### Person-centered outcomes (secondary)

Mobility will be assessed using the Aged Care Funding Instrument (ACFI) [20] module 2 developed by the Department of Health and Ageing. This component of the ACFI relates to the participant’s usual day-to-day assessed care needs with regard to mobility. Mean mobility scores will be compared between groups. ACFI data will be collected regularly by residential care facility staff.

Vision-specific QoL will be measured using the Impact of Vision Impairment for Residential Care (IVI-RC). The IVI-RC is a 28-item questionnaire developed to measure the impact of vision impairment on activity limitation and emotional wellbeing, and has been adapted specifically to the aged care setting by the study team from the original 28-item IVI questionnaire [21, 22].

Depressive symptoms will be determined using the Cornell Scale for Depression in Dementia (CSDD) [23]. This measure was chosen due to its suitability for use with individuals with moderate cognitive functioning. The interviews focus on depressive symptoms and signs occurring during the week before the interview. The final ratings of the CSDD represent the rater’s clinical impression. Each item is rated for severity on a scale of 0–2 (0 = absent, 1 = mild or intermittent, 2 = severe). The item scores are added together. Scores of 0–8, 9–13, 14–18, and 19–38 indicate no or minimal, mild, moderate, and major depressive symptoms [24].

Regarding falls rate, residential care settings have an incident reporting system (which varies from paper based to computerized systems) where any incident including falls will be recorded. Falls data will be retrieved from incident reporting systems in the participating residential care facilities and the proportion of falls will be compared between groups.

Health-related QoL will be assessed using the five-dimension EuroQoL (EQ-5D-3L) [25], a descriptive system that covers five dimensions (Mobility, Self-care, Usual Activities, Pain/Discomfort, and Anxiety/Depression). The EQ-5D-3L raw data can be converted to utilities, which will be used for our economic analyses.

With regard to utilization of visual devices (distance and near vision glasses; low vision aids), at the two- and six-month follow-up visits, participants in the intervention arm who have been prescribed spectacles or low vision aids, will be asked to self-report on how often the device has been used during the week, for how long it was used, and for what tasks.

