### Statistical analysis

The primary and secondary outcomes will be assessed using an intention-to-treat analysis applied to individual participants and repeated using the per-protocol sample (only participants who complete the clinical trial including the second assessment). To compare the effectiveness of ROC with usual care, presenting and best corrected near and distance VA (primary outcome) at the two- and six-month follow-ups will be analyzed and the differences from baseline VA will be used to investigate changes. The near and distance VA change is expected to be normally distributed and analysis of covariance will be used to compare the difference, adjusting for baseline values. Effect sizes for both groups will be calculated using Cohen’s d coefficient [27]. To determine the effectiveness of ROC on secondary outcomes, a Multivariable General Linear Model will be used to compare differences at two and six months from baseline on the IVI-RC, EQ-5D-3L and CSDD. If the EQ-5D-3L data are skewed, a multivariable quantile regression model will be used. Falls data will be compared across intervention and usual care groups at six months using a negative binomial regression if the data are over-dispersed. Changes in mobility will be analyzed using Mann–Whitney U tests. The difference in utilization of distance and near vision glasses and low vision aids between the treatment groups will be compared using the Chi-squared test and the utilization time will be compared using Student’s t-test or non-parametric test if appropriate. A multi-level model with a random intercept parameter will be utilized to account for within cluster correlations. All analyses will be performed using STATA version 15 (StataCorp. 2017. Stata Statistical Software: Release 15. StataCorp LLC, College Station, TX, USA).

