### Cost-effectiveness analysis

We will perform an incremental cost-effectiveness analysis from the payer perspective. Direct intervention costs (labor, material and supplies, and contracted services costs) associated with delivering the intervention over the one-year period will be collected and follow a cost collection approach described elsewhere [29]. The incremental costs of the intervention will need to account for any vision services received by the usual care group and any differences in costs for non-vision related services that may be an indirect result of the intervention. Information will be collected for any participants who fall or are hospitalized, transferred to high care or die. Aggregating these costs over the six-month period and adding them to the direct costs of the ROC intervention group, will allow the total medical costs for the intervention and the usual group to be quantified. The incremental cost-effectiveness ratio (ICER) will be calculated using the estimated mean difference in effect (EQ-5D-3L) and the estimated mean difference in costs between the intervention and the control groups. The ICER indicates the average incremental cost to gain one additional quality-adjusted life year (QALY). Cost data are likely to be skewed. Therefore, using non-parametric bootstrapping, 1000 replicates [30] will be generated to estimate the 95% confidence intervals around the ICER. A cost-effectiveness acceptability curve (CEAC) [31] will be used to show the probability that the intervention is cost-effective for a range of monetary values that a decision maker might be willing to pay for a unit change in QALYs. Cost-effectiveness will initially be quantified assuming that QALYs are only sustained for one year, but an assessment will also be made based on the assumption that they continue to accrue each year for the expected remaining life years in the study sample. Additional one-way (and n-way) deterministic sensitivity analyses will be performed to examine the effect of changing one (or n) of the model parameters.

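### The secondary outcome named as eye care utilization is replaced by use of glasses and low vision aids, and the between-arm test of that substitute has no planned control-arm data

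*Protocol article*

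**What the plan says.** The Abstract (Methods/design) states: "Secondary outcomes will include vision-specific quality of life, mobility, falls, depression, and eye care utilization at two and six months". The aims in the last paragraph of the Background make the comparison explicit, listing "depressive symptoms, rate of falls, and eye care utilization, compared to the usual care group at the two- and six-month visits".

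Under Person-centered outcomes (secondary), the only utilization outcome is introduced as "With regard to utilization of visual devices (distance and near vision glasses; low vision aids), at the two- and six-month follow-up visits", and the sentence goes on to say who is asked: "participants in the intervention arm who have been prescribed spectacles or low vision aids, will be asked to self-report on how often". The questions cover frequency of use, length of use and the tasks concerned.

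The Statistical analysis section then says: "The difference in utilization of distance and near vision glasses and low vision aids between the treatment groups will be compared using the Chi-squared test". Time of use is compared by a t-test or a non-parametric alternative.

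Use of eye care services appears elsewhere only under Cost-effectiveness analysis: "The incremental costs of the intervention will need to account for any vision services received by the usual care group".

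**The concern.** Receiving eye care and using a device are different things. A resident can be examined, referred or operated on and leave without a device. A resident can also wear glasses every day without having seen an eye care provider since baseline. The Background gives limited access to services as the reason why vision impairment stays common in aged care, so whether ROC changes the use of services is a natural question, and it is one that the aims commit to.

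If the outcome and analysis sections are followed as they stand, that question would be answered with a measure of device use. The measure itself is planned in one arm only, so it cannot supply the promised comparison with usual care either.

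**Working it through.** No arithmetic applies. The plan states no utilization rate, denominator or target difference, and its enrolment figure of 395 is built on visual acuity. The check is to set the sections side by side.

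1. **Construct.** The Abstract and the aims name eye care utilization. None of the outcome sections defines an outcome by that name. The one utilization outcome concerns glasses and low vision aids. It is assessed at the same two and six months, so it appears to stand in for the named outcome.

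2. **Test.** The tests given for utilization concern device use and time of use. No test is given for examinations, referrals, surgery or low vision appointments.

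3. **Who supplies the data.** The device questions go to residents who meet two conditions: they are in the intervention arm, and they were prescribed spectacles or a low vision aid. No usual-care resident meets the first condition. The planned test between treatment groups therefore has one arm with data and one without.

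4. **Who is not captured.** The Intervention section lists four options: refraction and spectacles, cataract surgery, ophthalmologist referral, and low vision rehabilitation. Two of the four (surgery and ophthalmologist referral) need not lead to a device. ROC residents treated only in those ways fall outside the device questions. So does every usual-care resident who takes up the referral described under Usual care.

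5. **Where services do appear.** The cost analysis must "account for any vision services received by the usual care group". That is an input to incremental cost, aggregated over six months. It is not an outcome compared between arms, and no two-month cut is mentioned.

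Points 1 and 2 show that the named objective has no outcome-level test. Point 3 shows that the substitute cannot be tested between arms as described.

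**The case against.** The strongest reply is that this article condenses protocol version 2.2, and that the schedule of assessments (Fig. 2) is not shown. A definition of service use could sit in the full protocol or in an analysis plan. That would answer a complaint about missing detail. It does not answer this one: the article names one construct as the objective, and then fixes a different construct with its own respondents and tests. An analysis plan faithful to those sections would carry the mismatch forward.

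A second reply is that vision is tested in both arms with whatever correction the resident presents with, so glasses could be noted for usual care too. The plan does not make this the utilization measure, and it would not give time of use.

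A reader might infer that residents treated by surgery or by an ophthalmologist will be counted as non-users. The documents do not support that. Residents without a device are simply not asked, and whether they are then excluded, missing or scored as zero is not stated. The Intervention section also says "participants will be eligible to receive more than one intervention pathway (e.g. spectacles and low vision rehabilitation aids/services", and the Cataract surgery section provides for spectacles after surgery where needed, so some of these residents would be device users. The number treated with no device at all is unknown.

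A reader might also want this outcome to check the allowance of about 10% for non-compliance in the sample size. A trial need not test such an allowance. Usual care itself includes a referral, so any contact in that arm would mix assigned care with self-sought care.

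It is fair, too, that the cost analysis names no contact-level source, so the data for a service-use outcome cannot be assumed to exist already.

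**Conclusion.** The point stands in a limited form. Eye care utilization against usual care is a stated secondary objective. As written it is not tested as an outcome, and the device-use test that takes its place has no planned control-arm data. Residents treated without a device are not captured, which is different from being misclassified.

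The consequence is confined to one secondary outcome; the primary vision outcome and the other secondary outcomes are unaffected. No numerical size can be given, because the documents contain no rate of service use or device use in either arm. The conclusion rests on reading treatment groups in the Statistical analysis section as the two randomized arms, as the rest of that section does. It also assumes that no undisclosed schedule extends the device questions to usual care. Even if either assumption failed, the change of construct would remain. The sections should be brought into line, because a small change restores an objective that the trial has announced.

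**What to change.** In the Person-centered outcomes and Statistical analysis sections:

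- Define eye care utilization as at least one contact with an eye care service (optometry, ophthalmology or low vision service) between baseline and follow-up, recorded in the same way in both arms.
- Draw on the vision-service information that the cost analysis already needs, with contacts dated so that they can be cut at two and six months.
- Compare arms with a logistic model with a facility random intercept, in keeping with the plan's own provision for clustering. Show the result with and without the on-site ROC examination that the study itself delivers.
- Report device use as a descriptive measure in the ROC arm among those prescribed a device, and drop the between-arm device test. Alternatively, ask the device questions in both arms and state the denominator.
- Use the same term in the Abstract, the aims, the outcomes and the analysis.

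The cost is an outcome definition, one model, and possibly a contact date and a brief question at follow-up visits that are already planned. The contact rate in the ROC arm will be high by design, so the version that includes the on-site examination says little by itself; the version without it is needed for interpretation.

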**Discussion:**

The ROC study is the first multicentered, prospective, customized, and cluster randomized controlled trial in Australia to determine the effectiveness of a comprehensive and tailored eye care model for people residing in aged care facilities. Results from this trial will assist health and social care planners in implementing similar innovative models of care for this growing segment of the population in Australia and elsewhere.

**Trial registration:**

Australian and New Zealand Clinical Trials Registry, ACTRN12615000587505. Registered on 4 June 2015 – retrospectively registered.

**Electronic supplementary material:**

The online version of this article (10.1186/s13063-018-3025-5) contains supplementary material, which is available to authorized users.

## Background

Globally, around 223 million people have vision impairment (VI) or blindness [1]. VI will continue to be a major contributor to the global burden of disease as a result of the rapidly aging population, as this segment of the population has the highest incidence of ocular conditions [2]. Aging leads to a decline in visual acuity (VA), a measure of the eye’s ability to resolve fine detail, resulting from a deterioration of the visual function system. VI is a significant problem in older adults as it increases disability and the risk of falls [3–5] and reduces vision-specific functioning, emotional health, independence, and participation in activities of daily living [5, 6]. The prevalence of VI in aged care facilities is reported to be significantly greater than in community-dwelling older adults [7–9]. Up to 60% of aged care residents have VI [5], compared to 5% of older adults aged > 70 years living independently in the community [10].

The prevalence of VI in aged care settings remains high due to limited access to eye care services [11]. This is despite the major causes of VI in older adults, such as uncorrected (and under-corrected) refractive error and cataracts, being correctable or treatable [5, 11, 12]. Adequate refractive correction, for example, could improve vision in up to 50% of individuals in nursing home residents [13]. Furthermore, prospective studies have shown that residents who receive correction [11] or cataract surgery [13] demonstrate short-term improvements (two and four months after intervention) in vision, quality of life (QoL) and increased participation in activities of daily living. Benefits have also been reported for mental health outcomes, with fewer depressive symptoms and lower levels of distress found in residents following active treatment compared to those with no correction or surgery [11].

For ocular conditions that cause irreversible or progressive vision loss, such as age-related macular degeneration (AMD), glaucoma, and diabetic retinopathy (DR), remaining vision can still be maximized through the provision of low vision rehabilitation. Few well-designed studies have examined the impact of low vision rehabilitation in residential care settings. Longitudinal studies, however, in community-living older adults have found improvements in vision-related QoL and participation in daily activities following prescription of low vision devices [14, 15].

To date, no study has evaluated the impact of providing comprehensive eye care services to individuals with a broad spectrum of ophthalmic conditions and residing in aged care facilities. Therefore, we will implement a prospective, customized, multicentered, and cluster randomized controlled trial (RCT) to evaluate the clinical, person-centered, and cost-effectiveness of a new model of eye care. We will compare the effectiveness of Residential Ocular Care (ROC) with usual care on improving presenting and best corrected near and distance vision (primary outcome) at the two- and six-month follow-up visits. Secondary outcomes will assess the effectiveness of ROC on improving vision-specific QoL, daily functioning, health-related QoL, depressive symptoms, rate of falls, and eye care utilization, compared to the usual care group at the two- and six-month visits, after baseline, and quantify the cost-effectiveness of ROC at six months after baseline.

## Methods and design

A multicentered, prospective, and cluster RCT has been designed in accordance with the CONSORT statement and the Helsinki declaration. The study has been approved by the Royal Victorian Eye and Ear Hospital (RVEEH; reference number 15/1232H), Mercy Health (reference number R13-52 AC) and the Australian College of Optometry (ACO; reference number H14 001) Human Research Ethics Committees. This trial is subject to annual review and auditing by the RVEEH Human Research Ethics Committee. The trial has been registered with the Australian and New Zealand Clinical Trials Registry, number ACTRN12615000587505. The study design outlining the ROC intervention and standard treatment participant recruitment process is shown in Fig. 1. A Standard Protocol Items: Recommendations for Interventional Trials (SPIRIT) Checklist is provided as Additional file 1 and a flow diagram is included as Fig. 2.

**Fig. 1 Fig1:**
[figure not shown]
Participant flow and timeline for trial improving eye care in residential aged care facilities using the Residential Ocular Care (ROC) model

